## **9. Exclusion criteria**

Minors or persons who are not able to give their consent or who are physically or cognitively unable to attend training or understand German education are excluded. Also excluded are study participants (patients, caring family members and pharmacy staff) who do not give or withdraw their written informed consent.

## **10. Method of randomization**

The participating community pharmacies are continuously assigned to a randomization plan drawn up in advance. The randomization plan is created online at [www.randomization.com](http://www.randomization.com)

## **11. Study procedure**

The study will be carried out in community pharmacies with which other projects have already established cooperation. Prior to the start of the study, pharmacy staff will be informed of erroneous and correct administration of the different dosage forms (see inclusion criteria) known from the literature, the use of study materials, and the study procedure. After written informed consent of the head of the pharmacy and pharmacy staff, the pharmacies will be assigned to control or intervention group (cluster randomization). There will be exclusive control pharmacies and intervention pharmacies.

Pharmacy staff addresses potential study participants according to the inclusion criteria during daily routine in the community pharmacy. It is possible within the scope of this study to train the use of different dosage forms for the same patient or family caregiver. In order to identify a potential administration error, the pharmacy staff asks the patient or family caregiver to use the medicine (duration approx. 2-5 minutes). Such a demonstration is quite common in the context of the usual pharmaceutical counseling. The demonstration can be performed with the patient's drug itself or with a placebo. The pharmacy staff assesses a possibly incorrect administration by using a checklist defined in advance for a specific dosage form. Checklists and placebo materials are provided by the Department of Clinical Pharmacology and Pharmacoepidemiology. In the control group, pharmacy staff provides a standard consultation (duration approx. 3 minutes) followed by the provision of standardized information material, e.g. written step-by-step

instructions. In the intervention group, the staging algorithm (Fig. 1) is used to determine the individual level of the patient or caregiver according to the Transtheoretical Model. The stage "Maintenance", i.e. the permanent correct use of the drug, cannot be detected with this algorithm. The purpose of this model is to identify in particular those medicines users who are not aware of administration errors despite incorrect use of the drug and who may not be motivated to seek training or detailed counseling.

[figure not shown]

Figure 2. Staging Algorithm

Patients or caregivers who are in a “pre-action stage” (i.e., precontemplation, contemplation, and preparation) will be informed and trained by the pharmacy staff about the use of the drug according to their individual level (Table 1) (approximately 5-10 minutes).

Table 1. Possible level-specific interventions.

| Stage of change   | Study-specific definition | Possible intervention                                                          | Example                                                                                                                              |
|-------------------|---------------------------|--------------------------------------------------------------------------------|--------------------------------------------------------------------------------------------------------------------------------------|
| Pre-contemplation | Lack of error awareness   | e.g. create awareness of the problem, point out risks of incorrect application | Presentation of a risk score, information about possible consequences of incorrect application and advantages of correct application |
| Contemplation     | Aware of an error         | e.g. point out the risks of incorrect application, show possibilities          | Proposal for a training                                                                                                              |

|             |                                            |                                                                 |                                                                                                           |
|-------------|--------------------------------------------|-----------------------------------------------------------------|-----------------------------------------------------------------------------------------------------------|
| Preparation | Aware of an error, search for solutions    | e.g. standardized education materials for specific dosage forms | Education based on standardized information materials                                                     |
| Action      | Drug is administered correctly             | e.g. regular monitoring                                         | Follow-up visits with re-presentation of the application, assessment by the pharmacy staff and retraining |
| Maintenance | Drug is permanently administered correctly | e.g. regular monitoring                                         | Follow-up visits with re-presentation of the application and assessment by the pharmacy staff             |

Immediately after the training (intervention group) or after issuing the standardized instructions (control group), the drug application is checked again using the checklist. If errors continue to occur, there will be a corresponding retraining in the intervention group. In the control group, the patient or family caregiver is made aware of the errors verbally.

After the pharmaceutical consultation that can represent a standard situation in community pharmacies, the patients or caregivers are invited to participate in the follow-up visits. Study information is provided by the pharmacy staff or staff of the department of Clinical Pharmacology and Pharmacoepidemiology. If the patient or caregiver wishes to participate in the study and attests this by his written consent, his so far anonymized data will be pseudonymized. After inclusion in the study, patients and caregivers are asked to answer a sociodemographic questionnaire (duration approx. 5 minutes). In addition, e.g. finger strength and cognitive abilities may be considered as factors influencing the training success. Further data collection during follow-up visits is pseudonymized. Within the study, three follow-up visits will be planned at 1 month, 6 months and 12 months. Patients or caregivers are either referred to the follow-up at the pharmacy at the appropriate time or contacted by pharmacy staff or staff of the department of Clinical Pharmacology and Pharmacoepidemiology. Patients or caregivers can choose the preferred way of contacting, e.g. call, email or letter, prior to inclusion into the study. At follow-up visits the patient or family caregiver will be asked to demonstrate again drug administration, which is evaluated by the pharmacy staff or staff of the department of Clinical Pharmacology and Pharmacoepidemiology using the checklist. In the case of incorrect application, re-training takes place again. During the follow-up visits, patients and caregivers might be contacted by pharmacy staff or staff of the department of Clinical Pharmacology and Pharmacoepidemiology, e.g. by

[figure not shown]

telephone or in writing by e-mail or post to assess the satisfaction of the participants with regard to the study. The study procedure will be evaluated and, if necessary, adjusted in a pilot phase with regard to feasibility by study staff and pharmacy staff.

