## **8. Inclusion criteria**

Patients and family caregivers:

- Age >18 years
- Physical and cognitive ability to attend training
- Application of at least one of the following dosage forms to oneself or others: Eye drops, transdermal patches, tablets to divide, liquid oral preparations and/or capsules
- Written informed consent to study participation after oral and written clarification

Pharmacy staff:

- Written informed consent to study participate in the study after clarification in a written or oral form

Community pharmacies:

- Spatial requirements to enable confidential consultation

[figure not shown]

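### Staff who know their pharmacy's arm decide whom to approach, and no rule fixes which dosage forms are scored: the 6-month comparison is open to selection bias, and to form-mix bias if forms are pooled

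*Protocol*

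**What the plan says.** **Allocation and recruitment.** In Protocol section 11, once the head of the pharmacy and the staff have consented, "the pharmacies will be assigned to control or intervention group (cluster randomization"). It adds: "There will be exclusive control pharmacies and intervention pharmacies". Recruitment follows: "Pharmacy staff addresses potential study participants according to the inclusion criteria during daily routine in the community pharmacy". No consecutive-approach rule, recruiting period or record of users approached is given.

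**Dosage forms.** Section 8 requires "Application of at least one of the following dosage forms to oneself or others", and lists "Eye drops, transdermal patches, tablets to divide, liquid oral preparations and/or capsules". On users with more than one form, section 11 says: "It is possible within the scope of this study to train the use of different dosage forms for the same patient or family caregiver". It does not say which forms, or how many, are demonstrated.

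**Consent.** After the consultation, which differs by arm, "the patients or caregivers are invited to participate in the follow-up visits". Section 16 confirms that patients and caregivers receive the study information after the training.

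**Outcome and analysis.** Section 4 defines the primary outcome as a comparison of the error rate between the two arms at 6 months, with no mention of dosage form. Section 15 tests it by chi-square. Dosage form enters only a logistic regression of training success, which section 4 lists as secondary. The sample-size paragraph of section 15 nevertheless gives the number of administrations needed for one dosage form and says that the calculation is made at that level.

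**The concern.** Randomising pharmacies balances the pharmacies, in expectation. It does not balance the users whom staff recruit afterwards while knowing the arm. If staff in one arm tend to approach users who are more or less able, the 6-month error rates differ even if the training does nothing.

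The forms open a second route. Section 4 treats dosage form as a possible influence on training success and asks whether success differs by form. If harder forms make up a larger share in one arm and all forms are analysed together, that alone moves the arm's error rate. A larger sample does not remove a bias of this kind; it only makes the biased difference easier to declare significant.

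Consent after the arm-specific consultation adds a third opportunity for the arms to diverge, because willingness to return may depend on the counselling received.

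**Working it through.** **1. The plan's own figure, and what it refers to.** Inputs from Protocol section 15: success 32% versus 52%, alpha 0.05 (two-sided reproduces the figure), power 0.80 (printed as beta), ICC 0.02, drop-out 15%.

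- Two-proportion formula without continuity correction: 95 per group.
- Design effect 1 + (5 − 1) × 0.02 = 1.08. Then 95 × 1.08 = 102.6, rounded up to 103, and 103 / 0.85 = 121.2, rounded up to 122.
- Design effect 1 + (10 − 1) × 0.02 = 1.18. Then 95 × 1.18 = 112.1, rounded up to 113, and 113 / 0.85 = 132.9, rounded up to 133.

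Both stated figures reproduce. (They do so only when 5 and 10 are entered as administrations per pharmacy rather than pharmacies per group. That is a separate matter.) What matters here is that 122, with 103 evaluable, is the requirement for a single dosage form.

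**2. The two readings side by side.**

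| Reading | Basis | Selective approach of users | Different form mix |
|---|---|---|---|
| All forms pooled | Section 4 outcome; section 15 chi-square | can bias | can bias |
| Within one form | Section 15 sample size | can bias | contributes 0 |

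**3. Size of the mix effect if forms are pooled.** With no training effect,

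spurious difference = (error-rate gap between harder and easier forms) × (difference between arms in the share of harder forms).

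The protocol gives neither factor, so both are assumed: gaps of 20 to 40 points and imbalances of 10 to 30 points. The control error rate is set at 68% (1 − 0.32, from section 15), with half harder and half easier forms in control.

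- Gap 20 (78% and 58%), intervention share of harder forms 40%: 0.40 × 78 + 0.60 × 58 = 66.0. Difference 68 − 66.0 = 2.0 points.
- Gap 30 (83% and 53%), share 30%: 0.30 × 83 + 0.70 × 53 = 62.0. Difference 6.0 points.
- Gap 40 (88% and 48%), share 20%: 0.20 × 88 + 0.80 × 48 = 56.0. Difference 12.0 points.

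The range is therefore 2 to 12 points. The planned difference is 52 − 32 = 20 points, so this is 10% to 60% of it. An imbalance the other way gives the same sizes with the opposite sign.

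**4. Selective approach within a form.** The same identity applies, with more and less able users in place of easier and harder forms. The protocol offers no figure for either factor, so no number is given.

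**The case against.** **Staff choice of form is not stated.** A reader might infer that staff select which of a user's forms enter the trial. The protocol does not say so. The sentence in section 11 only permits several forms, and section 15 explains the permission by education on each patient's own drugs. This stands: what is documented is the absence of a rule, not a choice.

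**The time incentive is weaker than it looks.** A reader might set about 3 minutes of control counselling against 5 to 10 minutes of training and conclude that intervention staff will favour easy forms. The longer time applies only to users in a pre-action stage, not to every form. Section 11 also says that the staging model is meant to find users unaware of their errors, which could draw intervention staff towards harder cases. So neither the incentive nor its direction is established.

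**The sample size points to within-form comparisons.** If the primary analysis is made within one form, mix bias disappears. That is correct, but sections 4 and 15 do not carry it into the primary test, and selective approach remains.

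**Some protection exists.** Both arms are scored by checklist before counselling, so baseline differences among included users would be visible, and form and number of drugs enter a logistic regression. This regression is secondary and leaves the chi-square test unadjusted. A statistical analysis plan, not shown here, might stratify. It could not recover users who were never approached or forms that were never demonstrated.

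**Conclusion.** The point holds in a limited form. Users are recruited after allocation by staff who know the arm, with no rule for whom to approach or which forms to score, and consent follows the arm-specific consultation. Selective approach can bias the 6-month comparison on either reading of the primary analysis; form mix can bias it if forms are pooled. The outcome and test on one side and the sample size on the other do not agree on which reading applies.

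The 2 to 12 points rest wholly on assumed gaps and imbalances and apply only to a pooled comparison. The protocol gives no error rates by form, so it does not show that the forms differ in difficulty by any given amount. Its 32% success rate comes from an inhaler study, and inhalers are not an eligible form.

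A reader might go further and quote an inflated false-positive rate by putting these shifts into 103 evaluable administrations per arm. The documents do not support that: 103 is the number for one form, where there is no mix, and no pooled sample size is stated.

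**What to change.** In section 11, state identically for both arms that:

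- staff approach consecutive eligible users in recruiting periods set in advance;
- the form or forms demonstrated follow a fixed order list, applied to the eligible forms that the user applies (use, as in section 8, not only forms dispensed that day), and are recorded before the demonstration;
- the same form or forms are scored at 1, 6 and 12 months;
- an anonymous tally by arm is kept of users approached, passed over and declining follow-up. Section 16 already foresees using consultation data from people who do not join.

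In section 15, make the primary comparison within, or stratified by, dosage form, and word the section 4 outcome to match. This removes the mix effect directly and brings the test into line with the sample size.

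The cost is a printed list, a tally sheet and less freedom for staff to choose convenient cases. One limit remains: the tally shows selection through consent after the consultation but does not remove it.

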##### **Secondary outcomes**

- Rate of incorrect medication administration before and after patient education in the control and intervention group.
- Rate of incorrect medication administration during the course of follow-up visits.
- Influence of the consideration of the individual level according to the Transtheoretical Model [20] on the willingness to participate in a training, i.e. long-term (1, 6 and 12 months) correct drug use.
- Univariate and multivariate analyses to evaluate the influence of covariates such as dosage form, patient characteristics, the training person and the number of medicines on training success.
- Qualitative: feasibility of implementation in community pharmacies, satisfaction of patients and caregivers.

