## **15. Statistical method**

### **Statistical design**

The error rate of the intervention group will be compared to the error rate of the control group by the chi-square test. The error rate of the medication administration before patient education will be compared to the error rate after the training by the McNemar test. A  $p\text{-value} \leq 0.05$  is considered as statistically significant. Feasibility of the education method into the daily routine of the community pharmacy and the contentment of the patients and family caregivers will be analyzed qualitatively. The influence of co-variables like dosage form, patient characteristics, educating person and number of drugs on the education success will be determined by logistic regression.

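### As written, the same-day re-check appears to miss intervention users who were correct at baseline, so for one secondary outcome that arm's error rate can fall or stay level but cannot rise

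*Protocol*

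**What the plan says.** All users first demonstrate their medicine and are scored on a checklist (protocol, section 11). The arms then differ.

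- **Control pharmacies.** "In the control group, pharmacy staff provides a standard consultation (duration approx. 3 minutes) followed by the provision of standardized information material". No condition on the baseline result is attached.
- **Intervention pharmacies.** Users are staged. Those in precontemplation, contemplation or preparation "will be informed and trained by the pharmacy staff about the use of the drug according to their individual level". Table 1 defines the Action stage as "Drug is administered correctly" and gives as its example "Follow-up visits with re-presentation of the application, assessment by the pharmacy staff and retraining".
- **Re-check.** "Immediately after the training (intervention group) or after issuing the standardized instructions (control group), the drug application is checked again using the checklist".

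Section 4 lists as a secondary outcome "Rate of incorrect medication administration before and after patient education in the control and intervention group", and separately "Rate of incorrect medication administration during the course of follow-up visits". Under Statistical design, section 15 says that the error rate "before patient education will be compared to the error rate after the training by the McNemar test".

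**The concern.** McNemar's test compares two counts: pairs that go from incorrect to correct, and pairs that go from correct to incorrect. Both need a second measurement on everyone who had a first. If the second demonstration is triggered by training, and training goes only to users who are not yet correct, the intervention arm has no way to record a worsening. Every chance change from incorrect to correct is counted, and every chance change the other way is lost. In the control arm both directions are recorded and can offset each other.

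Two things are then at stake for this outcome. The within-arm result in the intervention group mixes any training effect with ordinary variation between two demonstrations. The contrast between arms sets a group selected for baseline error against an unselected one.

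**Working it through.** **1. Who is re-checked, on the text.**

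| Baseline result | Control pharmacy | Intervention pharmacy |
|---|---|---|
| Incorrect | Instructions issued, so re-checked | Pre-action, so trained and re-checked |
| Correct | Instructions issued, so re-checked | Action, no same-day training listed, so no trigger for a re-check |

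Nothing in section 11 says that untrained intervention users repeat the demonstration, and nothing in the protocol says how they enter the after rate.

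**2. Which outcome uses the re-check.** Section 4 gives the follow-up visits their own secondary outcome, so the after in the before/after outcome is most naturally the same-day re-check. The primary outcome is the between-arm error rate at 6 months. At follow-up visits users demonstrate again with no condition on stage.

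**3. The protocol's sample size, used here only for scale.** Inputs from section 15: success 32% and 52%, alpha 0.05 (taken as two-sided), power 80%, drop-out 15%, ICC 0.02. With the pooled chi-square formula and a mean proportion of 0.42:

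- n = [1.96·√(2·0.42·0.58) + 0.842·√(0.32·0.68 + 0.52·0.48)]² / 0.20² = 94.4, rounded up to 95 per group.
- Design effect 1 + (5 − 1)·0.02 = 1.08; 95·1.08 = 102.6, rounded up to 103.
- 103/0.85 = 121.2, rounded up to **122**, as stated. With 10 in place of 5 the same steps give 133, also as stated.

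This calculation does not involve the re-check and is not changed by this point. The figure of 122 is before drop-out, which is the right scale for a same-day measurement.

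**4. Illustration under no true effect.** The protocol gives no baseline error rate and no rate at which a repeat demonstration is scored differently. Both are assumed here:

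- 50% incorrect at baseline, so 61 of 122.
- A chance f that a repeat demonstration is scored the other way.
- Unmeasured intervention users counted as still correct.

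Improvements in the intervention arm are then X ~ Binomial(61, f), and recorded worsenings are 0. With all k changed pairs in one direction the exact two-sided p-value is 2·0.5^k: 0.0625 for k = 5 and 0.031 for k = 6. Significance therefore needs X ≥ 6. The uncorrected chi-square form has statistic k and needs k ≥ 4.

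| f | False gain, 61·f/122 | P(X ≥ 6), exact | P(X ≥ 4), uncorrected |
|---|---|---|---|
| 2% | 1.0 points | 0.1% | 3% |
| 5% | 2.5 points | 8% | 36% |
| 10% | 5.0 points | 58% | 87% |

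**5. The same switching with everyone re-checked.** Take 6 changes each way in 122. A fully re-checked arm shows 50.0% before and 50.0% after, with p = 1.00. If baseline-correct users are not re-checked, the counts are 6 against 0 and p = 0.031. The error rate then appears to fall from 50.0% to 55/122 = 45.1% if unmeasured users are carried forward as correct. Among re-checked pairs only, it falls from 100% to 55/61 = 90.2%. The direction is the same either way; the apparent size depends on which convention is used, and the protocol names neither.

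**The case against.** **The exclusion is inferred.** No sentence says that correct intervention users are not re-checked. The brackets in the re-check sentence can be read as fixing when it happens, not who is eligible. Table 1 is headed as possible interventions and its entries are examples, and the staging figure is missing from the text at hand. This stands as a limit on certainty: a reader might infer that the protocol rules out a re-check for Action users, and it does not. But if pharmacies may read the sentence either way, measurement can differ between sites, and the same edit cures that.

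**The primary result is safe.** This stands in full. A reader might infer that the trial's main comparison favours the intervention. The documents do not support that: the 6-month comparison, its sample size and the error rates at follow-up visits do not use the re-check.

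**The analysis can repair the contrast between arms.** This stands in part. Control data would contain the matching subset of users incorrect at baseline, so both arms could be restricted to it, and an analysis plan could say so. No analysis plan can supply the missing second measurement, so the within-arm intervention test and the whole-group after rate stay unrepaired.

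**The size is assumed.** This also stands. At a 2% flip rate false significance is about 0.1% by the exact test, well under the nominal 5%. The higher figures of 36% and 87% need the chi-square form without continuity correction; with the correction, six one-way pairs are again required. A baseline of 68% incorrect with a 10% flip rate would give larger numbers (6.8 points; 85% to 97%). Holding prevalence stable there, however, requires 8.3 of the 39 correct users, about 21%, to flip the other way, which is a strained assumption. No weight is put on that case.

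**Conclusion.** The point holds for one secondary outcome, the immediate before/after error rate. If section 11 is followed as written, the intervention arm's measured rate can fall or stay level but cannot rise, while the control arm's can move either way, and the two arms are measured in different populations. The direction of the bias follows from the procedure. Its size does not: about 1 to 5 points, with exact-McNemar false significance between about 0.1% and 58%, for assumed flip rates of 2% to 10%, half the users incorrect at baseline and unmeasured users counted as correct. These percentages should not be read as the trial's actual error rate. The reading that baseline-correct intervention users have no same-day second measurement rests on the section 11 text and Table 1, without the staging figure. The change is worth making because it is cheap and the measurement cannot be recovered afterwards; it is not a threat to the primary result.

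**What to change.** Amend the re-check sentence in section 11 so that every user in both arms repeats the scored demonstration at the end of the first contact, whatever the baseline checklist result or stage. Compute the before and after rates, and the McNemar test, on all of them. This alters measurement only, not who is trained. The cost is one further demonstration, put at 2 to 5 minutes in section 11, for intervention users who were correct at baseline, with the existing checklist.

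If the procedure cannot be changed, restrict the between-arm before/after comparison to users incorrect at baseline in both arms and say so in advance. The within-arm McNemar result in the intervention group should then not be read as a training effect.

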With methods respecting the individual level of the patients or family caregivers, progress to change their behavior may be positively influenced [20]. Thus, studies for improving the compliance show that considering the individual levels influences the outcome of the intervention positively [21]. The model has not been applied yet for trainings to avoid medication errors. Yet it seems to be obvious that patients or family caregivers, who do not realize a medication error because they have not been aware of it, do not recognize the necessity for training. To reach these patients and family caregivers and to motivate them for training, the Transtheoretical Model could be the theoretical framework for implementing training interventions.

According to this prospective randomized controlled study, standardized patient education in community pharmacies should be evaluated. The training method should consider the patients’ or family caregivers’ lack of awareness if necessary and particularly should be integrated in the daily routine of pharmacies. For this reason, the pharmacy staff of the particular community pharmacy will carry out the training and document any additional work required. Before the study is started, the pharmacy staff will be informed about incorrect and correct administration of the dosage form which is known from literature (see inclusion criteria), the use of education materials and the study procedure. There are three follow-up visits planned, approximately one month, six months and twelve months after the first patient education. Patients or family caregivers will either be addressed in the community pharmacy (recruiting and follow-up visits) or they will be contacted by employees of the participating community pharmacies or by an employee of the department of Clinical Pharmacology and Pharmacoepidemiology and they will

be invited into the correspondent community pharmacy (follow-up visits). The pharmacy staff or employees of the department of Clinical Pharmacology and Pharmacoepidemiology will again assess the quality of medication administration of patients or family caregivers during their follow-up visits to evaluate the sustainability of the first training.

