#### **4. Aims and issues of the project**

##### **Primary outcome**

- Rate of incorrect medication administration will be compared between control and intervention group at 6-month follow-up.

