##### **The following general questions are related to the project:**

- Is it possible to motivate patients or family caregivers to attend training by raising awareness of a drug administration error?
- Is the consideration of the individual awareness of the error an advantage in the training compared to a "normal" counseling?
- Is the training success sustainable?
- Is the patient education intervention feasible in the community pharmacy setting?
- Are any differences in training success depending on the dosage form or person?

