## **5. Method to be tested**

### **General description**

The influence of the individualization of patient education on the success of the training should be evaluated.

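### Error rates at 6 and 12 months cannot show whether the first training lasts, because users found incorrect at an earlier visit are re-trained

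*Protocol*

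**What the plan says.** Section 3 (Introduction) states that administration is assessed again at the follow-up visits "to evaluate the sustainability of the first training". Section 4 lists, among the general questions of the project, "Is the training success sustainable".

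The primary outcome in section 4 reads: "Rate of incorrect medication administration will be compared between control and intervention group at 6-month follow-up". One secondary outcome is "Rate of incorrect medication administration during the course of follow-up visits". Another links the Transtheoretical Model level to long-term correct use at 1, 6 and 12 months. Section 15 compares the groups' error rates with a chi-square test and describes the 12-month visit only qualitatively.

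Section 11 sets out what happens after an error. On the first day: "If errors continue to occur, there will be a corresponding retraining in the intervention group", whereas "In the control group, the patient or family caregiver is made aware of the errors verbally". For the follow-up visits the rule is: "In the case of incorrect application, re-training takes place again". This last sentence names no arm.

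**The concern.** A user who fails the checklist at 1 month is taught again before the 6-month assessment. If that user is correct at 6 months, the crude rate records a success, although the first session's effect had already gone by 1 month. The same happens between 6 and 12 months. A report that answered the sustainability question from these rates would credit the first session with results that may come from later teaching.

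There is also a smaller matter. The first-day rule separates the arms and the follow-up rule does not. If controls are re-trained too, the 6-month contrast may be diluted. If only the intervention arm is re-trained, the contrast includes a difference in follow-up contact as well as the stated object of study: "The influence of the individualization of patient education on the success of the training should be evaluated". A reader of the results needs to know which rule applied.

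**Working it through.** The protocol attaches no figure to this point, so there is none to reproduce. The check sets the visit schedule against the re-training rule.

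| Visit | What has preceded the assessment | Does the crude rate reflect the first session alone? |
|---|---|---|
| 1 month | First session, including the same-day action on remaining errors | Yes |
| 6 months | First session, plus any re-training at 1 month | No |
| 12 months | First session, plus any re-training at 1 and at 6 months | No |

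For users seen at both 1 and 6 months there are four possible histories:

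1. Correct, then correct: never re-trained at follow-up, and the skill was kept.
2. Correct, then incorrect: not re-trained before 6 months, and the skill was lost.
3. Incorrect, then correct: due for re-training at 1 month, so the later success may come from it.
4. Incorrect, then incorrect: failed at both visits.

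Let *c6* be the share correct at 6 months, *s* the share with history 1 and *g* the share with history 3. Then

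*c6* = *s* + *g*.

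The crude rate counts *g* as success. A measure of whether the first session lasted should count only *s*. Because only incorrect users are re-trained, re-training at 1 month cannot alter histories 1 and 2, so *s* is free of it.

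Some users in history 3 would have been correct at 6 months without re-training. Let *u* be the share who would be correct at 6 months after the first session alone. If re-training never turns a would-be correct user into an incorrect one, then

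*s* ≤ *u* ≤ *c6*

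within each arm. So *s* is a conservative measure of durability and *c6* a generous one. The width of the interval is *g*, which the linked checklist data will show. The protocol gives no value from which *g* could be forecast.

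On the arm rule, three places bear on the follow-up sentence in section 11. The word *again* points back to the first-day rule, which gives retraining to the intervention arm. Table 1 lists retraining at follow-up under the Action stage, and staging is used only in the intervention arm. Section 5 (Effects/risks) has staff explain the error and the correct use to any user who misuses the drug, without naming an arm. Together these favour re-training in the intervention arm only, with an explanation for controls, but none of them says so outright.

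**The case against.** The strongest reply is that a measure derived from data already collected belongs in the statistical analysis plan, which is not shown. The phrase about the first training occurs once, in the Introduction; the question in section 4 speaks of training success generally. Table 1 treats follow-up retraining as part of the level-specific intervention, so the design already tests the whole strategy. Lasting correctness is also not foreign to the protocol: section 4 mentions long-term correct use at three time points, and Table 1 has a Maintenance stage.

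Much of this stands. The protocol does have the idea of lasting correctness, though it gives no rule for deriving it. The whole-strategy reading of the primary outcome is right. What remains is a conflict inside the protocol between the stated purpose of the visits and the re-training rule. An analysis plan could add the better measure, but it could not make the crude 6-month rate mean what the Introduction says.

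A second objection concerns the replacement. Counting every 1-month failure as a failure penalises users who would have corrected themselves, and a rule is needed for users who miss the 1-month visit. Both are fair and are dealt with in the fix.

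On the arm rule, the text already leans one way, and restricting re-training to one arm is partly a design choice. That part is only a clarification.

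**Conclusion.** The crude error rates at 6 and 12 months cannot answer the durability question as the Introduction frames it. This follows from the visit order and the re-training rule alone, and assumes only that some users are incorrect at an earlier visit and are re-trained as planned. The practical weight falls on 6 months, since 12 months is only described. The change should be made, but the trial does not depend on it.

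A reader might infer that the primary comparison is biased. The document does not support that: the groups are randomised, and the 6-month contrast is a valid comparison of whole strategies. A reader might also infer a definite loss of power or a definite distortion of the 20-point planning difference. Neither can be calculated, because any figure would rest on an invented 1-month error rate and an invented effect of re-training. Limits on *s* worked out from the planning success rates of 32% and 52% would not help either. They hold for any two yes/no measurements and would be the same if nobody were re-trained.

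**What to change.** 1. Keep the 6-month primary comparison, and describe it as the effect of the whole strategy, including re-training at follow-up.
2. Assess the durability of the first training from the 1-month rate and from the share correct at 1 month and still correct at 6 months, comparing the randomised groups on the linked checklist data. A user incorrect at an earlier follow-up visit counts as a failure. A user who missed the 1-month visit had no re-training there and is classified by the 6-month result. Treat 12 months in the same way, descriptively.
3. State which arm is re-trained at follow-up. The reading the text favours is re-training in the intervention arm, with controls told of the error and the correct use as section 5 provides. If the sponsor wants re-training in both arms, the protocol should say that instead.

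The cost is a few sentences, with no added visits, staff or form items. The durability measure is conservative, because users who would have corrected themselves count as failures. Users who missed the 1-month visit have one fewer occasion to fail, so attendance at that visit should be reported by arm. The claim for the first session becomes narrower. Under intervention-only re-training, the primary result has to be read as including the difference in follow-up contact.
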